### Platelet counting

Ethylenediaminetetraacetic acid (EDTA) anti-coagulated venous blood and cord blood will be used for the platelet counting in the mothers and their babies, respectively.

### Anti-HPA antibody screening, identification and titration

The Monoclonal Antibody Solid Phase Platelet Antibody Test (MASPAT) Kit will be used in the screening of potential anti-HPA antibody-positive pregnant women [9]. The anti-HLA antibody and the anti-HPA antibody will be further distinguished by chloroquine-treated (i.e., HLA-depleted) platelets [4]. Two-fold serum dilutions in phosphate-buffered saline from undiluted to one in 1024 will be done to determine the titre of the anti-HPA antibody. Antigen specificity will be confirmed by LIFECODES Pak Lx (Immucor) [10].

### Diagnosis and grading of NAIT

NAIT is defined as a platelet count in the neonates of less than 150 × 10^9^/L and the HPA is incompatible with the mother. When the platelet count is less than 50 × 10^9^/L, we will grade the NAIT as severe. These cases are distinguished from cases of moderate (platelet count 50 × 10^9^ - 100 × 10^9^/L) or mild NAIT (platelet count 100 × 10^9^-150 × 10^9^/L) [5].

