**Methods:**

A multicentre, prospective cohort study design will be used, and 55,497 pregnant women will be recruited for the first screening of the anti-HPA antibody at 12 to 28 weeks of gestational age. Subjects who are positive in the first screening for the anti-HPA antibody will be included in the exposure group. Re-tests of the antibody titre, antigen-specificity and genotyping of HPA and HLA will be conducted during admission. A ratio of 1:1 paired individuals with the same ethnicity and parity but testing negative for the anti-HPA antibody will be randomly selected to be included in the non-exposure group. NAIT will be diagnosed in the newborns on day one of the birth. The HPA of the neonates in the exposure group will also be genotyped by sequencing. Associations of maternal HLA with the occurrence of the anti-HPA antibody and correlation of the severity of NAIT with the titre of the anti-HPA antibody will be further analysed.

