### Recruitment and informed consent

The study is being conducted at 24 Grade-A Tertiary Hospitals in China. Subjects testing positive in the anti-HPA antibody test at 12-28 weeks of gestation will be included in the exposure group. A ratio of 1:1 paired individuals with the same ethnicity and parity but negative in the anti-HPA antibody test will be randomly selected to be included in the non-exposure group. The investigators will inform the participants about all aspects about the trial. The informed consent will include permission to collect blood samples from the mothers and their infants for antibody screening and genotyping of HPA and HLA, gathering data from their medical records and the storage of biological samples for a maximum of 10 years for additional analyses related to the current study. The participants will be informed that trial participation is voluntary and that they are free to withdraw at any time. All the investigators are aware of the guidelines for good clinical practice [8].

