### Variable and potential confounders

The primary outcome variables will be the titre of the anti-HPA antibody of the mothers and the platelet count of the newborns. The secondary outcome variables will include the pregnancy number. The potential confounding variables that will be measured will include nationality, maternal history (e.g., parity, still birth and abortion), allogenic platelet transfusion history and diseases leading to a decreased platelet count in the mother (e.g., idiopathic thrombocytopenic purpura, eclampsia and gestational diabetes mellitus) and in the newborns (e.g., intrauterine growth retardation, intrauterine infection and neonatal asphyxia).

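### Neither primary case definition uses the antigen specificity the study collects, so the antibody rate may be overstated and the NAIT rate may be biased in either direction

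*Protocol article*

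**What the plan says.** All references are to the protocol article.

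- **Case definition** (Diagnosis and grading of NAIT). The count criterion reads "NAIT is defined as a platelet count in the neonates of less than 150" (in units of 10^9/L). The second criterion is worded "and the HPA is incompatible with the mother". The rule does not mention the mother's antibody or its target.
- **Exposure** (Abstract, Methods): "Subjects who are positive in the first screening for the anti-HPA antibody will be included in the exposure group". Recruitment and informed consent agrees: "Subjects testing positive in the anti-HPA antibody test at 12-28 weeks of gestation will be included in the exposure group".
- **Assays** (Anti-HPA antibody screening, identification and titration): the MASPAT kit "will be used in the screening of potential anti-HPA antibody-positive pregnant women". Then "The anti-HLA antibody and the anti-HPA antibody will be further distinguished by chloroquine-treated (i.e., HLA-depleted) platelets". Specificity is confirmed with Pak Lx.
- **Timing** (Study procedure and data collection): titre and specificity are tested at admission for delivery in women who were positive. HPA genotyping is done for antibody-positive mothers and their infants.
- **Role of specificity** (Table 1): a secondary objective only. The two primary objectives are the antibody rate and the NAIT rate among antibody-positive women.
- **Other causes of low counts** (Variable and potential confounders): these are to be measured. For newborns the examples are "intrauterine growth retardation, intrauterine infection and neonatal asphyxia".

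**The concern.** The Background describes NAIT as the result of maternal IgG against an incompatible antigen carried on the foetal platelets. The operative definition is looser. Take a mother with anti-HPA-5b whose infant lacks HPA-5b but differs from her at another HPA system. If that infant's count is low because of infection or asphyxia, the rule as written calls it NAIT.

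The exposure definition has a related gap. The screening section treats MASPAT positives as provisional and adds two further steps. No sentence says which of those steps decides that a woman is antibody-positive, or what happens to a woman whose specificity is not confirmed.

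Both primary results depend on these definitions. The study is meant to supply baseline figures for China and to inform screening. If misclassification is built into the counts and its direction is unknown, readers cannot correct for it afterwards.

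**Working it through.** **1. The plan's own figures** (Determination of sample size). Inputs: NAIT 16.7% in antibody-positive and 2.5% in antibody-negative women, α 0.05, β 0.1, antibody rate 0.19%, dropout 10%.

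- The two-proportion formula, two-sided, gives 88.35, so 89 per group. 89 × 1.1 = 97.9, which rounds to the stated 98.
- 98 / 0.0019 = 51,578.9, against the stated 51,578.
- The precision formula with a back-solved δ of 0.2 × 0.0019 = 0.00038 (δ is not stated) gives 1.96² × 0.0019 × 0.9981 / 0.00038² = 50,451. Multiplied by 1.1 this is 55,496, against the stated 55,497.

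The sample-size arithmetic reproduces and is not the problem.

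**2. A model for the two errors.**

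- T = 16.7%: NAIT rate among women with a true antibody (the plan's figure, taken as true).
- b = 0.025 × m: chance of a low count from another cause together with some HPA mismatch. The 2.5% is the plan's figure, and m is the chance of any mismatch.
- f: share of women classed as positive who have no HPA antibody.

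The documents give neither m nor f. The values below are assumptions that span a range.

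Observed NAIT rate = (1 − f)[T + (1 − T)b] + f·b = T + (1 − T)b − f·T(1 − b).

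Observed antibody rate = 0.19% / (1 − f).

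**3. Case rule alone (f = 0).** The excess is (1 − T)b. Its maximum, at m = 1, is 0.833 × 0.025 = 0.0208, or 2.1 points. With 55,497 × 0.9 × 0.0019 = 95 exposed women, that is 95 × 0.0208 = 2.0 infants.

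**4. Both errors together.**

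| f | Antibody rate | NAIT rate, m = 0.1 | m = 0.5 | m = 1 |
|---|---|---|---|---|
| 0 | 0.19% | 16.9% | 17.7% | 18.8% |
| 10% | 0.21% | 15.2% | 16.1% | 17.2% |
| 20% | 0.24% | 13.6% | 14.4% | 15.5% |
| 50% | 0.38% | 8.6% | 9.5% | 10.6% |

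**5. Break-even.** Setting the observed NAIT rate equal to T gives f = (1 − T)b / [T(1 − b)]. This is 1.3% at m = 0.1, 6.3% at m = 0.5 and 12.8% at m = 1. Below that share of false positives the NAIT rate is biased upward, and above it downward.

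**The case against.** **The chloroquine step is aimed at the obvious false positives.** This stands. It should remove women who react only through anti-HLA antibody, so the documents do not support reading exposure as an unverified raw screen. The plan cites the same Japanese study for this method and for the 0.19% rate, so 0.19% may already reflect a similar algorithm. What remains open is whether the step comes before group assignment.

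**Specificity may be known earlier than admission.** The Abstract and the Follow-up section describe the admission tests as repeats, which could imply earlier testing. This also stands, so the point does not rest on timing. It rests on specificity entering neither definition.

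**The condensed article may mean the targeted antigen.** That is plausible given the Background. The case rule is nevertheless stated outright, and applied literally it accepts any mismatch.

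**Other causes of low platelets are measured.** They are, and how they enter the analysis is detail for the full plan. Their absence from the case rule does not show that they are ignored.

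**The case-rule effect is small.** It is: at most 2.1 points, against sampling error of 1.96 × √(0.167 × 0.833 / 95) = ±7.5 points. But it is systematic and cheap to remove.

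**Requiring Pak Lx confirmation would lose antibodies outside the panel.** This stands. Confirmed status should not become the only primary definition.

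**Conclusion.** The point holds as a defect of definition. The NAIT rule does not tie the mismatch to the maternal antibody, and the collected specificity enters neither primary definition.

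The loose case rule can raise a 16.7% NAIT rate by at most 2.1 points. This assumes that the 2.5% the plan gives for antibody-negative women can serve as the background rate of low counts. The plan labels that figure NAIT, so this is an interpretation. Any false positives left after the chloroquine step raise the antibody rate and lower the NAIT rate.

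A reader might infer that both primary rates are inflated. The documents do not support that. False-positive women enter the denominator of the NAIT rate, and under the assumed values of m the net bias turns downward once about 1% to 13% of exposed women are false positives. The antibody rate is overstated only to the extent that false positives remain, and the documents give no figure for that.

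**What to change.** 1. Define NAIT as a count below 150 × 10^9/L in an infant who carries the antigen recognised by the mother's identified antibody. Report low counts without that match as a separate category.
2. State that the chloroquine-distinguished result determines antibody-positive status, for both the antibody rate and the exposure group.
3. Report the antibody rate and the NAIT rate twice: for all such positives, and for those with Pak Lx-confirmed specificity.
4. Add a sensitivity analysis that excludes newborns with another listed cause of low platelets.

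The cost is low. Maternal specificity, mother and infant HPA genotypes and the confounders are already to be collected, so the change is wording plus slightly more analysis. The drawback is that the confirmed rate misses antibodies outside the panel, which is why the two sets of figures should stand side by side.

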### Diagnosis of ICH

For all newborns with thrombocytopenia, an ultrasound diagnosis will be further performed to determine ICH.

### HPA and HLA genotyping

HPA genotyping will be performed with BioArray HPA BeadChips (IMMUCOR) [11]. HLA genotyping of DRB1, DRB3, DRB4, DRB5, DPB1 and DQB1 will be conducted through PCR-SBT (polymerase chain reaction - sequence based typing) (SBT*excell*erator®).

### Follow-up

There will be two follow-up visits after recruitment. One will be at the end of pregnancy before delivery, in which re-tests of the antibody titre, antigen-specificity and genotyping of HPA and HLA will be conducted in the mothers. The second follow-up will be after delivery, in which platelet counting and HPA genotyping of the newborns will be performed and NAIT will be diagnosed and graded.

### Variable and potential confounders

The primary outcome variables will be the titre of the anti-HPA antibody of the mothers and the platelet count of the newborns. The secondary outcome variables will include the pregnancy number. The potential confounding variables that will be measured will include nationality, maternal history (e.g., parity, still birth and abortion), allogenic platelet transfusion history and diseases leading to a decreased platelet count in the mother (e.g., idiopathic thrombocytopenic purpura, eclampsia and gestational diabetes mellitus) and in the newborns (e.g., intrauterine growth retardation, intrauterine infection and neonatal asphyxia).

### Statistical analysis

The data will be analysed using SPSS V18 (SPSS, Chicago, Illinois, USA). 95% confidence levels will be set to test for significance. Descriptive statistics will be used to analyse the general data, the positive incidence of the anti-HPA antibody and the morbidity of NAIT. The frequency of thrombocytopenia between groups will be compared by using the χ^2^ test. The χ^2^ test will also be used in the analysis of the associations between the pregnancy number (or mother HLA genotype) and the incidence of the anti-HPA antibody. The correlations between the titre of the anti-HPA antibody and the severity of NAIT will be analysed by using the multiple regression analysis.

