## Background

Neonatal alloimmune thrombocytopenia (NAIT) is caused by maternal immunoglobulin G (IgG) antibodies raised against incompatible human platelet alloantigen (HPA) carried on foetal platelets. Foetal platelets are sensitized by anti-HPA IgG and destroyed by the monocyte-phagocyte system [1]. Although many cases are mild, NAIT is one of the most frequent causes of severe thrombocytopenia (platelet count <50 × 10^9^/L) and intracranial haemorrhage (ICH) [2].

The HPA is highly polymorphic. Currently, 35 HPA antigens have been indexed in the Immuno Polymorphism Database (IPD) (http://www.ebi.ac.uk/ipd/hpa/). The antigen type of HPA varies according to ethnicity, which directly causes differences in the incidence and antigen-specificity of anti-HPA antibodies and the morbidity of NAIT. In Caucasian populations, the majority (>75%) of NAIT cases are due to fetomaternal incompatibility of HPA-1a [3]. In contrast, anti-HPA4b and anti-HPA5b are the main causes of NAIT in the Japanese population [4]. The incidence of NAIT is 1 in 1000 in Caucasians [5] and 1.5 in 1000 in Japanese subjects [4].The consequence of NAIT in women with HPA-4b or HPA-5b is less severe than that in Caucasian women with anti-HPA-1a. Generalized purpura and even ICH have been found in HPA-1a-incompatible neonates [2]. In the Japanese population, purpura has been found to develop rarely in HPA-4b-incompatible infants and not to develop in HPA-5b-incompatible infants [4].

It has also been reported that the presence of HPA antibodies is tightly associated with human leukocyte antigen (HLA). Among these antibodies, the most well known is HLA-DRB3*0301, which is strongly associated with alloimmunization to HPA-1a [6, 7]. The immunization rates also correlate linearly with the number of pregnancies. The anti-HPA antibody (mainly against HPA-4b and HPA-5b) has been found in only 0.19% (95% CI: 0.11-0.28%) of women in their first pregnancy and in 1.97% (95%CI: 1.41-2.54%) of women in their fourth or subsequent pregnancies [4].

Few data have been reported regarding the incidence and antigen-specificity of the anti-HPA antibody, the morbidity of NAIT and clinical outcomes among Chinese patients. Therefore, this study seeks to provide these baseline data on NAIT caused by anti-HPA antibodies in pregnant Chinese women.

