## Methods/design

This study is a nationwide, prospective, non-interventional, multicentre cohort study. The objectives are listed in Table 1. The survey and data collection will provide baseline data on NAIT in China and help form an appropriate clinical screening procedure.

**Table 1 Tab1:** Study objectives

Primary objectives	
• The positive incidence of the anti-HPA antibody in pregnant Chinese women.	
• The morbidity of NAIT in anti-HPA antibody-positive pregnant women in China.	
Secondary objectives	
• Antigenic specificity of anti-HPA antibodies.	
• Association of the anti-HPA antibody with HLA genotype.	
• The relationship between the titre of the anti-HPA antibody and the clinical symptom severity of NAIT.	

This study is non-interventional. The assignment of subjects to antenatal treatments (such as intravenous immunoglobulin and intrauterine fetal platelet transfusion) or a particular delivery planning is not decided in advance but instead falls within current practice.

Study recruitment started primarily at the sponsor centre at The Second Affiliated Hospital of The Third Military Medical University on 1 November 2016. All other centres initiated consecutive recruitment before the end of January 2017. Recruitment is expected to be completed before December 2018.The goal is to enrol 55,497 women at 12-28 weeks of gestation.

The study subjects will be pregnant Chinese women and their newborns. Inclusion and exclusion criteria are listed in Table 2. Subjects with NAIT in a previous pregnancy or a positive family history of first degree relatives will not be excluded but will be analyzed hierarchically.

**Table 2 Tab2:** Inclusion and exclusion criteria

Inclusion criteria
• Pregnant women 18–50 years of age
• Pregnant women at 12-28 weeks of gestation between 1 January 2017 and 31 December 2018.
• Willingness of the mother to give birth in a participating hospital
• Willingness to participate in the study
Exclusion criteria
• Pregnant women unwilling to participate in the study
• Pregnant women planning to prematurely terminate the pregnancy

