### Study procedure and data collection

All healthy pregnant women receiving regular care at the obstetrical outpatient department of participating hospital will be counselled and asked at 12-28 weeks of gestation to participate in this study. General information will be collected and the anti-HPA antibody evaluation will be conducted after informed consent is received. The test of the antibody titre and antigen-specificity will be conducted at the production admission if the anti-HPA antibody test is positive. Genotyping of HPA will be further completed for anti-HPA antibody-positive mothers and their infants. Genotyping of HLA will be performed for mothers in both the exposure and non-exposure groups. Platelets of their newborns at day one of the birth will be counted, NAIT and ICH will be diagnosed.

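### The antibody-rate objective is national, but only a descriptive rate from 24 tertiary hospitals is planned, and an unweighted overall figure would follow the recruited pregnancy-number mix

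*Protocol article*

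**What the plan says.** All references are to the protocol article.

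- **Target.** Methods/design, Table 1, lists as the first primary objective: "The positive incidence of the anti-HPA antibody in pregnant Chinese women". The same section describes the scope: "This study is a nationwide, prospective, non-interventional, multicentre cohort study".
- **Sample.** Recruitment and informed consent: "The study is being conducted at 24 Grade-A Tertiary Hospitals in China". Study procedure and data collection describes those approached: "All healthy pregnant women receiving regular care at the obstetrical outpatient department of participating hospital". Table 2 adds that the mother must be willing to deliver in a participating hospital. Recruitment is consecutive. No sampling frame or weighting is described.
- **Analysis.** Statistical analysis: "Descriptive statistics will be used to analyse the general data, the positive incidence of the anti-HPA antibody and the morbidity of NAIT". The same section plans a chi-squared test of antibody incidence against pregnancy number.
- **Sample size.** Determination of sample size treats the rate as one simple proportion, with 0.19% as the planning value.
- **What drives the rate.** The Background, citing Japanese data, puts the rate at 0.19% for first pregnancies. For higher pregnancy numbers the same source found the antibody much more often: "in 1.97% (95%CI: 1.41-2.54%) of women in their fourth or subsequent pregnancies". On ethnicity the Background says: "The antigen type of HPA varies according to ethnicity, which directly causes differences in the incidence and antigen-specificity of anti-HPA antibodies".
- **Variables collected.** Variable and potential confounders lists pregnancy number as a secondary outcome variable, and nationality, parity and abortion history among the confounders. Women with NAIT in a previous pregnancy, or with a first-degree family history, are to be analysed separately (Methods/design).

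**The concern.** The target is a national figure, the sample is not a probability sample of Chinese pregnancies, and the named analysis contains no step that links the two. This would matter little if the rate were much the same in all women. The article's own Background says it is not: the rate rises about tenfold from first to fourth-or-later pregnancies. An overall proportion is then an average of stratum rates, and its weights are the recruited shares. If women at tertiary hospitals differ from all pregnant women in pregnancy number, the estimate is centred elsewhere than on the national rate. A larger sample narrows the interval but does not move the centre.

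The result is offered as baseline data for China and as an aid in judging whether antenatal screening is needed, so where it is centred is of practical importance. The sample-size section shows the same gap: its rate for all women, 0.19%, is the value that the Background gives for first pregnancies only.

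**Working it through.** **1. The plan's own figure.** Formula: n = Z²p(1−p)/δ², with Z = 1.96 and p = 0.0019. The article does not state δ. Taking δ = 0.2p = 0.00038 gives n = 3.8416 × 0.0019 × 0.9981 / 0.00038² = 50,451.3. Multiplying by 1.10 for dropout gives 55,496.5, which rounds up to the stated 55,497. The implied half-width is 0.038 percentage points at a rate of 0.19%.

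**2. The gradient.** 1.97 / 0.19 = 10.4.

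**3. Intermediate strata (assumption).** The Background describes the relation as linear in the number of pregnancies but gives only the two end rates. The step is (1.97 − 0.19)/3 = 0.593 points, so the rates for pregnancies 1, 2, 3 and 4+ are 0.19, 0.783, 1.377 and 1.97%.

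**4. Two assumed mixes.** The documents give none; these are illustrations.

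| Mix (1/2/3/4+) | Calculation | Overall rate |
|---|---|---|
| 55/30/10/5% | 0.1045 + 0.2350 + 0.1377 + 0.0985 | 0.576% |
| 40/30/20/10% | 0.0760 + 0.2350 + 0.2753 + 0.1970 | 0.783% |

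The difference is 0.207 points and the ratio is 1.36.

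**5. Sampling error for comparison.** At 0.576% and n = 55,497: 1.96 × √(0.00576 × 0.99424 / 55,497) = 0.063 points. The gap between the two mixes is about 3.3 times this (0.207/0.063).

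**6. How large a difference in mix would matter.** Under the linear assumption, moving a share of women from first to second pregnancy shifts the overall rate by 0.593 points times that share. A shift of one half-width needs 0.063/0.593 = 10.6 percentage points of women.

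**7. Check without interpolation.** Mix only the two strata that the article reports. With 5% fourth-or-later pregnancies the rate is 0.95 × 0.19 + 0.05 × 1.97 = 0.279%, which is 0.089 points above the first-pregnancy rate. The half-width at 0.279% and n = 50,452 (the number before the dropout allowance) is 0.046 points.

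**8. Uncertainty in the gradient.** Using the confidence limits that make the gradient smallest (0.28% and 1.41%), the step is 1.13/3 = 0.377 points. The mean number of steps above a first pregnancy is 0.30 + 2 × 0.10 + 3 × 0.05 = 0.65 in the first mix and 0.30 + 2 × 0.20 + 3 × 0.10 = 1.00 in the second. The gap becomes 0.35 × 0.377 = 0.13 points, still larger than the half-width.

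**The case against.** The strongest reply is that descriptive statistics is a broad term in a condensed article. It does not rule out standardised or stratum-specific rates, and the choice of reference weights may be left to the full protocol or analysis plan. That is right as far as it goes: a reader might infer that a crude pooled rate has been fixed as the sole estimate, but the article never says so. That inference rests on the term used and on the one-proportion sample size. What remains is that the article itself states the national target, the hospital sample and the method, and these do not match as written.

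Other parts of the reply also stand:

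- Pregnancy number is not ignored. The planned chi-squared analysis tabulates the stratum rates. It tests whether they differ, however, and does not recentre the overall figure. The separate analysis of women with a NAIT history does not do so either.
- A reader might conclude that the Chinese result could not be compared with the Japanese one. This is not so: the Japanese rates are quoted by pregnancy number, and the planned breakdown allows a like-for-like comparison.
- The mixes are assumed, and the second doubles the combined share of third and later pregnancies from 15% to 30%. They show that the effect can be large, not that it is.
- It is tempting to set the implied planning margin of 0.038 points against an overall rate near 0.58%, so that a shift of 0.038/0.593 = 6.4 percentage points of women would exhaust it. That margin belongs to a rate of 0.19%. The same 20% relative margin at 0.576% is 0.115 points and needs a shift of about 19 percentage points.
- The ethnic contrast in the Background is between Caucasian and Japanese populations. No figure shows variation within China.
- Recruitment is consecutive and all eligible women in regular care are to be asked, so describing the sample as self-selected volunteers would go too far.

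**Conclusion.** The point holds in limited form. The article names a national rate as its target but fixes only a descriptive analysis of women recruited at 24 tertiary hospitals. On its own evidence the rate depends strongly on pregnancy number, so an unweighted overall proportion would estimate the rate for the recruited mix.

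The documents do not support the stronger conclusion that the estimate will be biased by a known amount or in a known direction, because they give neither the hospital nor the national mix. The illustrative shift of about 0.2 points, against a half-width of about 0.06, rests on three assumptions: that the Japanese gradient carries over to China, that the rate is linear between the two reported values, and that the two invented mixes are plausible. The first is one the plan itself leans on, since its sample size uses the same source. The change is worth making because it is cheap and the variables are already collected. Making the standardised rate the sole primary estimate is debatable and is not required.

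**What to change.** In Statistical analysis, add that the overall antibody rate will be reported in three forms, each with a 95% CI:

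1. the unweighted rate in the recruited women;
2. the rates by pregnancy number (or by parity);
3. a rate directly standardised to the national distribution of that same variable, with ethnicity added where national weights exist.

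The strata and the weights must use the same variable. Pregnancy number and birth order differ, since abortions and stillbirths count towards the first only. If only birth-order weights can be obtained, use parity strata and say that this does not fully remove the pregnancy-number effect. Standardising on these variables also does not correct for other ways in which tertiary-hospital patients may differ.

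If no suitable weights can be found, state the result as the rate in women attending the participating tertiary hospitals, and word the objective and conclusions to match.

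The cost is a few lines of text, one set of external weights, a little more analysis and a slightly wider interval for the standardised rate. No new data or participants are needed.

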**Discussion:**

The study is expected to provide baseline data on NAIT in China. Besides, we hope to find out a population who expresses particular HLA molecules has significant higher risk of HPA alloimmunization in Chinese individuals. We also hope to find a Chinese-specific cut-off antibody titre for the prediction of the severity of NAIT and to provide a means to evaluate the necessity of antenatal treatment.

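### HLA is typed only in matched pairs, yet its link with the antibody is planned as an unmatched chi-square test against incidence, which this sample cannot give directly

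*Protocol article*

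**What the plan says.** **Sampling.** Under Recruitment and informed consent, women who screen positive form the exposure group. For the comparison group, "A ratio of 1:1 paired individuals with the same ethnicity and parity but negative in the anti-HPA antibody test will be randomly selected".

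**Typing.** Study procedure and data collection limits HLA typing to these two groups: "Genotyping of HLA will be performed for mothers in both the exposure and non-exposure groups". The section on HPA and HLA genotyping lists six loci: "HLA genotyping of DRB1, DRB3, DRB4, DRB5, DPB1 and DQB1 will be conducted through PCR-SBT".

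**Analysis.** The Statistical analysis section assigns the χ² test to "associations between the pregnancy number (or mother HLA genotype) and the incidence of the anti-HPA antibody". The general rule is that "95% confidence levels will be set to test for significance". No paired, stratified or conditional method is named for these tests. The section does not say whether HLA is tested by locus, genotype or allele, or in which sample pregnancy number is tested.

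**Aim.** The HLA association is a secondary objective (Table 1). The abstract hopes to identify "a population who expresses particular HLA molecules has significant higher risk of HPA alloimmunization".

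**The concern.** For the HLA objective, antibody status is the outcome and HLA type is the factor. Women are selected on the outcome and matched on ethnicity and parity, so this is a pair-matched case-control comparison. Three consequences follow.

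1. A plain χ² test treats the two groups as independent. If a matching factor is related to HLA carriage, the unmatched odds ratio lies nearer to 1 than the odds ratio within matched sets, and power is lost.
2. Half of the typed women are antibody-positive because the sample was built that way. The proportion positive among carriers of an allele is therefore not an incidence. The sample supports odds ratios, or HLA frequencies in positives and negatives.
3. The same sentence covers pregnancy number. If that test were run in the parity-matched pairs, the matching would largely remove the effect under study.

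At stake is the size and reliability of the HLA result, which the Discussion calls a key point of the study.

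**Working it through.** **Inputs from the article (Determination of sample size).** NAIT 16.7% against 2.5%; α 0.05; β 0.1; 10% dropout; 98 antibody-positive subjects; antibody rate 0.19%; 55,497 women recruited.

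**Assumptions, not in the article.** Two ethnic groups, their shares among the pairs, and HLA carriage in each. These are varied below.

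**1. The number of pairs reproduces.** With p̄ = (0.167 + 0.025)/2 = 0.096, two-sided α and 90% power:

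n = (1.96 × √(2 × 0.096 × 0.904) + 1.2816 × √(0.167 × 0.833 + 0.025 × 0.975))² / 0.142² = (0.8166 + 0.5182)² / 0.02016 ≈ 88.4, so 89.

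89 × 1.1 = 97.9, so 98, as stated. Also 98/0.0019 = 51,578.9, against the stated 51,578. I use 98 pairs below.

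**2. Attenuation.** Let carriage in negatives be q in an ethnic group, with a within-group odds ratio of 3. Carriage in positives is then 3q/(1 − q + 3q). Matching gives both arms the same ethnic mix. Worked case, shares 70/30, q = 0.10 and 0.50:

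- Positives: 0.30/1.20 = 0.25 and 1.50/2.00 = 0.75.
- Pooled negatives: 0.7 × 0.10 + 0.3 × 0.50 = 0.22.
- Pooled positives: 0.7 × 0.25 + 0.3 × 0.75 = 0.40.
- Unmatched odds ratio: (0.40/0.60)/(0.22/0.78) = 2.36.

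Power is from simulation of 98 pairs at the 5% level:

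| Minority share | Carriage, majority / minority | Unmatched OR (true 3) | Power, χ² | Power, McNemar |
|---|---|---|---|---|
| 10% | 20% / 20% | 3.00 | 94% | 94% |
| 10% | 10% / 30% | 2.87 | 83% | 84% |
| 30% | 10% / 50% | 2.36 | 82% | 87% |
| 30% | 5% / 60% | 1.89 | 51% | 74% |

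In the last scenario with no true association, the χ² test rejects in 1.4% of runs. Ignoring the pairs makes it conservative.

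**3. Incidence by HLA type.** Expected positives: 55,497 × 0.0019 ≈ 105. Expected negatives: 55,497 − 105 = 55,392. Drawing 105 of them is a sampling fraction of 105/55,392 ≈ 0.19%. Positives are 50% of the typed sample, against 0.19% of the cohort.

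**4. Pregnancy number.** The Background cites antibody rates of 0.19% in first and 1.97% in fourth or later pregnancies, a ratio of 1.97/0.19 ≈ 10. Pairs with the same parity cannot show most of such a gradient. The full screened cohort can.

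**5. Multiplicity (secondary).** For k independent tests at 0.05 the familywise error is 1 − 0.95^k: 26.5% for k = 6, 79% for k = 30, 95% for k = 59. Simulation with 98 pairs and six unlinked loci gave 46% for 12 allele tests and 77% for 30. Complete linkage, in effect one locus with about 10 alleles tested, gave about 40%.

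**The case against.** The strongest reply is that the practical loss may be small. The article gives neither the ethnic mix nor HLA carriage by ethnic group, and in the mild scenario the two tests are almost equal in power. Where they differ, the unmatched test errs toward caution. The article also uses the word incidence loosely and plans a test of association, not a table of risks by HLA type. This stands as a limit on the size. It does not make the named test fit the design, and an unseen analysis plan would not make the correction unnecessary, because the published text commits to the test.

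Stronger readings are tempting, but the documents do not support them:

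- **False HLA associations are almost certain.** That needs roughly 59 independent tests. The article gives no number of alleles and no unit of testing, and linkage between loci lowers the figure. Silence on a multiplicity rule is not evidence that none exists, since an analysis plan may hold it.
- **Odds ratios will be attenuated.** This happens only if carriage differs by a matching factor.
- **All antibody specificities are pooled.** The article does not say so; specificity is determined and is an objective of its own.
- **The thrombocytopenia comparison is biased.** The plan states that "The frequency of thrombocytopenia between groups will be compared by using the χ^2^ test". There the matching is on exposure, so it does not bias the crude comparison of risks. Ignoring the pairs costs mainly precision.
- **The pregnancy-number test is invalid.** An ordinary χ² test in the full screened cohort is valid. The article only fails to say which sample is meant.

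**Conclusion.** The point holds in limited form. From the text alone, an unmatched test is fixed for matched case-control data, and the quantity named cannot be read directly from a sample that is 50% positive by design.

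The size of the first defect is conditional. A true odds ratio of 3 falls to between about 2.9 and 1.9 in the scenarios where carriage differs, and stays at 3 where it does not. The loss of power runs from about 1 percentage point to 23 (74% − 51%). These figures rest on assumed ethnic shares and carriage and on 98 pairs. The second defect needs no outside assumption.

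The multiplicity risk is real but secondary: 26.5% for six independent locus-level tests, more if testing is by allele. The analysis should be changed. The concern touches a secondary objective and does not threaten the estimate of antibody frequency in the screened cohort.

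**What to change.** - **HLA:** analyse the matched sets by conditional logistic regression or McNemar's test (exact or Firth methods if sparse), or stratify by ethnicity and parity.
- **Measure:** report odds ratios in place of incidence. If absolute risk by HLA type is wanted, reweight the negatives by their sampling fraction, taken within ethnicity and parity strata because selection was matched on both.
- **Pregnancy number:** state that it is tested in the full screened cohort.
- **Multiplicity:** state the unit of HLA testing, apply Holm or false-discovery-rate control, and label allele-level results exploratory.

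No new data are needed, provided that pair identifiers are kept and ethnicity and parity are recorded for all screened women. The cost is revised wording and slightly more analysis, and fewer alleles will be called significant. Where carriage does not vary with the matching factors, the paired analysis costs almost no power (94% for both tests).
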